## Abstract

**Background:**

Evidence suggests chemotherapy treatment for breast cancer is associated with side effects such as cognitive impairment in domains of memory, attention, concentration and executive function. Cognitive impairments reported by patients have been associated with higher levels of emotional distress. To date, intervention studies to alleviate cognitive impairment associated with chemotherapy have focused on psycho-educational techniques or cognitive training. Studies have not yet considered physical activity as a potential for alleviating cognitive problems. Physical activity interventions are reported to be effective in alleviating emotional distress and fatigue in those with breast cancer. They have also been reported to improve cognitive functioning in the elderly, in those suffering with dementia and in children. We propose that physical activity could also help to alleviate cognitive impairments in women diagnosed with breast cancer. The study has been designed using a recently developed taxonomy of behaviour change techniques to reliably report the content of the intervention to allow future replication.

**Method:**

This study will deliver a home-based moderate intensity walking intervention to women diagnosed with breast cancer mid-way through their chemotherapy treatment and will compare them to patients receiving usual care alone. The primary outcome measure for this intervention is changes in an objective measure of memory assessed using the Digit Span. Secondary outcome measures include: objective measures of executive function; attention; visual spatial skills; self report cognitive function; self-report fatigue; anxiety; depression; mood and self-esteem. As emotional distress has been associated with self-reporting of cognitive problems, this intervention will further test whether emotional distress mediates between the amount of walking undertaken during the intervention period and levels of self-reported cognitive functioning.

**Discussion:**

The development of an effective intervention for preventing difficulties in emotional and cognitive functioning of cancer patients’ post-treatment will help to guide health care professionals to improve patients’ overall quality of life. It will also provide direction for future research, ultimately to improve the day to day functioning of breast cancer survivors.

**Trial Registration:**

Current Controlled Trials ISRCTN50709297.

## Background

Breast cancer is one of the most frequently diagnosed cancers in the UK [1]. Between 15% to 75% of patients treated by chemotherapy experience problems with their cognitive functioning as well as physical and emotional side effects [2,3]. Multiple cross-sectional and longitudinal studies over the last decade have found associations between chemotherapy and cognitive impairments, both subjectively reported and objectively measured, in a proportion of breast cancer patients and survivors [4-10]. Commonly reported cognitive impairments include difficulties with memory, attention, information-processing speed and executive function [11,12]. Studies suggest that around 71% of patients report problems with memory and 64% report difficulties with concentration [13,14]. In addition, patients receiving chemotherapy were 2.25 times more likely to show cognitive decline following chemotherapy in comparison with the control group [13]. The effects of chemotherapy on cognitive function among breast cancer patients can be long-term with impairments evident between 4 months to 20 years post-treatment [15-19]. Cognitive decline following chemotherapy for breast cancer can have a profound negative impact on patients’ overall quality of life [13,15,20,21].

Evidence suggests that cognitive problems are more frequently reported by patients than that objectively measured using neuropsychological assessments. Literature suggests that subjective reporting and objective measurements of cognitive decline are not associated with one another [5,6,9,10,22-27] but both are associated with poorer functional outcomes and psychosocial well-being, which may be a predisposing risk factor for developing cognitive impairment following chemotherapy in those with breast cancer. [5,6,13,20,22,23,25,26,28-34].

The above studies suggest the need for evidence-based interventions to prevent cognitive decline experienced by breast cancer patients during chemotherapy. However, very few interventions have been implemented to address cognitive difficulties and have yielded mixed results. For example, Poppelreuter et al. [35] found no intervention effects through the implementation of cognitive training strategies whereas Von Ah et al. [36], who also used cognitive training, reported improvements in self-reported cognitive functioning, better mental health and quality of life outcomes. Ferguson et al. [37] implemented a cognitive behavioural therapy intervention and found no significant effect on self-reported cognitive function [37]. Schuurs et al. [38] delivered a psycho-education programme on cognitive strategies by using goal setting and problem solving techniques. They found positive improvements in the management of objective and subjective cognitive function, psychosocial distress and social functioning in patients with a range of cancer diagnoses [38].

The interventions discussed above were implemented between 12 to 8 months after the completion of treatment. However, evidence suggests that patients report difficulties with cognitive functioning half way through their treatment [39,40]. Evidence suggests that interventions to manage the side effects of chemotherapy would be beneficial to patients mid way through treatment as 75% of patients experience cognitive decline during treatment with 35% of patients continuing to report cognitive problems post-treatment [41]. Therefore, more efforts should be made towards preventing cognitive problems during treatment when it is most prevalent.

The benefits of physical activity among cancer patients are well documented with regards to managing treatment related symptoms such as fatigue, regaining physical functioning, improving quality of life [42,43] and for improving physical functioning and fitness for breast cancer patients [44-51]. A meta-analysis of 28 studies revealed positive effects of exercise on cancer related fatigue both during and after treatment [52]. Physical activity reduced distress and improved fatigue and energy levels at three month follow up [51-53]. Physical activity rehabilitation has also shown to improve levels of anxiety for those affected by breast cancer [54]. Evidence demonstrates promising effects of low to moderate levels of physical activity as a protective strategy for preventing cognitive impairment in healthy individuals, children and the elderly [55-59]. In light of this evidence we hypothesise that moderate levels of physical activity may also help in protecting breast cancer patients against chemotherapy-induced cognitive impairment. Hospital-based and/or supervised interventions can restrict participation as patients undergoing chemotherapy are often busy with treatment schedules, are unwell or have limited access to exercise facilities due to transportation or scheduling difficulties [44]. Therefore, home-based interventions which do not restrict participation may be more feasible and increase adherence.

To summarise, there is good evidence illustrating the benefits of physical activity rehabilitation for cancer patients. However, the effects of physical activity on cognitive functioning for those diagnosed with cancer have not yet been examined. Current studies implementing physical activity as a form of rehabilitation for breast cancer have focused upon the benefits it has on physical fitness, quality of life, fatigue and emotional distress. Very little research has been conducted to explore the effects of physical activity upon cognitive functioning in breast cancer patients. Therefore, the current intervention aims to investigate the effects of a self-prescribed moderate intensity walking on cognitive functioning and emotional well-being of adjuvant and neo-adjuvant breast cancer patients.

## Methods

### Objectives/hypothesis

The primary aim of the study is to investigate the effectiveness of a home-based moderate intensity walking intervention on reducing cognitive impairment of breast cancer patients receiving chemotherapy. Our primary hypothesis is that women who complete the physical activity intervention will demonstrate less impairment in memory in comparison to women in the non-intervention group. Our secondary hypotheses are that the intervention group will perform better than the control group on objective and subjective measures of cognitive function, and will report better quality of life outcomes than the control group. Furthermore, within the intervention group, emotional well-being will mediate between physical activity level and level of subjectively reported and objectively tested impairment in memory, attention and concentration.

### Design

The study is a randomised controlled trial comparing the home based walking intervention group with care as usual control group. Outcomes will be assessed at two time points: mid-way through chemotherapy (pre-intervention) and after the completion of chemotherapy (post-intervention). All participants will also complete outcome measures prior to receiving chemotherapy to familiarise them with study materials, study setting and the researcher.

### Recruitment

Sixty two females with a primary diagnosis of breast cancer will be recruited from the Leicester Royal Infirmary (31 participants per group). Patients who have been diagnosed, are waiting to begin adjuvant or neo adjuvant chemotherapy and are considered fit to take part in moderate intensity exercise by their oncologist will be invited to participate in the study by the researcher. Oncologists will subjectively assess patients’ suitability for the study based upon their medical history and physical presentation during the consultation. Those interested in participating then meet with the researcher who will provide them with an information sheet and explain the study in further detail. Those participants who show interest are then followed up a week later at which point they are asked to complete a consent form. Participants will be assessed using objective measures of cognitive functioning in a small room near the waiting area. They will also complete a series of self-report questionnaires in the comfort of their own homes and return them using the pre-paid envelope provided.

### Inclusion criteria

The researcher will assess patients to ensure they meet the following inclusion criteria: to be female; aged 18–75 at diagnosis; have a primary diagnosis of stage I to III breast cancer; receiving chemotherapy and are able to speak and read English.

### Exclusion criteria

Patients will not be eligible for the intervention if they meet the following exclusion criteria: previously diagnosed with cancer; those who currently exceed the recommended guidelines of 30 minutes of moderate intensity exercise five times a week; breast cancer is a secondary diagnosis and have a current psychiatric disorder.

### Randomisation

Eligible participants will be block randomised using four blocks to ensure equal numbers of patients in both groups as recruitment will be staggered. Within each group of four patients, two will be allocated to the intervention group and two to the control group at time two (mid way through chemotherapy). There is no masking of participants or the research team.

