### Procedure

The researcher will recruit participants, collect cognitive and psychosocial data at pre and post-intervention and facilitate the delivery of the physical activity intervention. Initially, consenting participants will be asked by the researcher to complete a self-report cognitive functioning questionnaire, a battery of objective tests of cognitive impairment and a questionnaire pack assessing quality of life and emotional well-being pre-chemotherapy to allow familiarisation with the researcher and research materials. They will be asked to wear ActiGraph GT3X+ accelerometers for 10 hours a day for 7 days for a measure of habitual walking after the familiarisation assessment [63]. These data will be collected prior to receiving chemotherapy.

After completing two cycles of chemotherapy, participants will be asked to complete the same measures again at the clinic. Patients will then be randomised to either the intervention or control group following the procedures outlined above. The walking intervention starts after 2 cycles of treatment in line with recommendations from oncologists who suggests that the intervention will be better received by patients after they have had 2 cycles of chemotherapy and understand what they are facing with regard to treatment side effects. The intervention group will be asked to commit to the 12 week walking intervention and will be provided with a booklet outlining the amount of walking they should take part in alongside guidance and tips on how to incorporate this into their daily routines. The intervention group will also be asked to commit to a minimum of 150 minutes of moderate intensity walking per week for the duration of the 12 week intervention, in line with recommended guidelines [61]. They will be told how to monitor their own intensity levels and will be encouraged to aim to walk at moderate levels of intensity for 150 minutes a week for the duration of the intervention. Walking schedules will be self-prescribed by participants but the researcher will recommend that they begin by completing 10 minutes of walking at any one time and then steadily increase the duration of walking to 30 minutes. Participants will be provided with a pedometer for the duration of the intervention and will be asked to log their walking for the 12 week period. Those randomised to the control group will continue to receive usual care alone.

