### Sample size

Sample size for the study was calculated based upon previously published data [37,38] and Cohen’s Power Primer [74]. According to a prospective calculation, for a repeated measures ANOVA, 26 participants per group are required to detect a large effect size with power of 0.80 and α set at .05. It is reasonable to assume a large effect size in this population based upon previous research [37,38] and their memory performance on the digit span. Allowing for 20% attrition due to withdrawal and illness we aim to recruit 31 patients per group.

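### Fixed, unmasked blocks of four let about a third of allocations be foreseen when the same researcher gives the pre-intervention tests

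*Protocol article*

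**What the plan says.** The Randomisation section of the protocol article states: "Eligible participants will be block randomised using four blocks to ensure equal numbers of patients in both groups as recruitment will be staggered". Read alone, this could mean four blocks in all, but the next sentence shows that blocks of four are meant: "Within each group of four patients, two will be allocated to the intervention group and two to the control group". No variation in block size is mentioned. The section ends: "There is no masking of participants or the research team".

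The Recruitment section gives 62 women from one hospital, 31 per group. No stratification factor is named, so the text describes a single sequence.

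On who does what, the Procedure section says: "The researcher will recruit participants, collect cognitive and psychosocial data at pre and post-intervention and facilitate the delivery of the physical activity intervention". The Inclusion criteria section adds: "The researcher will assess patients to ensure they meet the following inclusion criteria". Fitness for exercise is judged by the oncologist.

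On timing, consent and a familiarisation assessment come before chemotherapy. The measures are repeated after two cycles, and then: "Patients will then be randomised to either the intervention or control group following the procedures outlined above". Under Statistical analyses, this time-two assessment is the pre-intervention level of the within-subject factor in the 2x2 models.

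**The concern.** In a fixed 2:2 block of four, the fourth allocation always follows from the first three, and the third follows from the first two whenever those match. Working this out takes only the block size, which the article publishes, and the past allocations, which an unmasked researcher who helps deliver the intervention will know. Concealing the list does not prevent it.

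The consequence is specific to this design. The time-two scores are one of the two measurements from which the treatment effect is formed. In a two-arm, two-time model the group-by-time effect is the difference between arms in change. A shift in the pre-intervention score linked to the coming arm therefore passes straight into the effect estimate. Digit span, the primary measure named in the Abstract, is given face to face, so pace, prompting and encouragement could vary with what the tester expects. A secondary route is the order in which women who have reached time two are randomised.

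**Working it through.** **The plan's own figures.** The article gives no figure for predictability. Its only calculated figure is the sample size: "26 participants per group are required to detect a large effect size with power of 0.80 and α set at .05". Assuming d = 0.8 and a two-sided test (sidedness is not stated), the noncentral t distribution gives power 0.791 at 25 per group and 0.807 at 26, so 26 reproduces. It does not bear on the rest of the check.

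**Inputs.** Block size 4, split 2:2, unmasked (Randomisation). N = 62, one hospital (Recruitment). Assumption: the observer knows every earlier allocation when each new woman is tested.

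**Allocations known with certainty.** A 2:2 block has 6 equally likely orders.
- AABB and BBAA force the last two allocations.
- The other four orders force only the last.
- Forced allocations per block: (2 × 2 + 4 × 1)/6 = 1.333, and 1.333/4 = 33.3%.
- For 62 patients there are 15 full blocks plus 2 patients. The first two places of a block are never forced, so the count is 15 × 1.333 = 20, and 20/62 = 32.3%.

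**Best-guess accuracy.** The chance that the best guess is right, by place in the block, is 1/2, 2/3, 2/3 and 1. The third is (1/3 × 1) + (2/3 × 1/2) = 2/3. The sum is 2.833, and 2.833/4 = 70.8% in full blocks. Over 62 patients: (15 × 2.833 + 1/2 + 2/3)/62 = 43.67/62 = 70.4%. Simple randomisation gives 50%.

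**What a foreseen allocation could do to the estimate.** By symmetry the 20 forced allocations split on average 10 per arm, or 10/31 = 32% of each arm. If each foreseen intervention patient's pre-intervention score were shifted by s, the between-arm contrast in change would move by about 0.32s. If foreseen controls were shifted equally in the opposite direction, it would move by about 0.65s. The documents give no value for s.

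**Alternative block sizes.** A fixed block of size 2m has 2m/(m + 1) forced places: 1.5 of 6 (25%) for size 6 and 1.6 of 8 (20%) for size 8. For randomly varied sizes, 4,000 trials of 62 patients were simulated. Sizes were equally likely, and the observer knew the possible sizes but not the block boundaries.

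| Block sizes | Known with certainty | Best guess right |
|---|---|---|
| 4 fixed | 32.2% | 70.4% |
| 2, 4, 6 | 4.0% | 70.1% |
| 4, 6 | 5.6% | 69.1% |
| 4, 6, 8 | 2.4% | 67.9% |

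Varying the sizes removes most of the certainty but little of the guessing advantage. Including size 2 gives back most of that small gain.

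**The case against.** The strongest reply is that the usual selection route is largely closed. Inclusion criteria are mostly objective, the oncologist judges fitness, and consent comes before chemotherapy, with randomisation only after two cycles. At consent, a woman's own later arm can hardly be foreseen. No re-screening at time two is described, and the timing of time two is tied to the chemotherapy cycles, which leaves limited room to reorder women. This stands, and it narrows the point mainly to the conduct of the time-two tests.

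There are also partial safeguards. Randomisation already follows the time-two measures, questionnaires are filled in at home, and the attention test is computerised. The pre-chemotherapy assessment was made when allocation could hardly be foreseen, so it offers some check on a distorted time-two score. It would be too strong to say that nothing in the data could reveal a problem. None of this covers the digit span as it is given at time two.

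A reader might infer three further things that the article does not support.
- *That the researcher runs the randomisation or holds the list.* The text is passive and names nobody. Who generates and holds the list is detail an article may leave to the full protocol, so its absence is no fault.
- *That women are being selected into arms, or that bias has occurred.* The text shows exposure only.
- *That the aim of equal groups fails because 62 is not a multiple of four.* A 32:30 split is trivial, and varying the block sizes would not cure it.

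**Conclusion.** The point holds as a modest weakness in a stated design choice. Fixed blocks of four, open allocation and one researcher in all the contact roles make about 20 of 62 allocations (32%) certain in advance and about 70% guessable. The main exposure is the time-two testing that supplies the baseline of the 2x2 analysis; the order of randomisation is a lesser one.

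The 32% assumes a single unstratified sequence, an observer who knows the block size, and each woman tested after all earlier women have been allocated. If several women are tested before any of them is randomised, fewer allocations are foreseeable at testing. The size of any resulting bias cannot be worked out from the document.

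**What to change.** Replace the fixed block of four with block sizes varied at random, for example 4, 6 and 8, avoiding size 2. Do not disclose the sizes to the researcher, and do not publish them while recruitment is open. Keep the stated order of events and make it explicit that each allocation is released only once that woman's time-two scores have been recorded.

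This cuts allocations known with certainty from about 32% to about 2% (about 6% with sizes 4 and 6). Best-guess accuracy falls only from about 70% to about 68%, so the change should be described as reducing predictability and not as removing it.

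The cost is a new list before the next randomisation and a possible final imbalance. With sizes 4, 6 and 8, the worst case is stopping half-way through a block of 8 with four more women in one arm: 33:29, against 32:30 at worst under the present scheme.

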### Intervention

In line with previous literature [60] the intervention will consist of 12 weeks of home-based moderate intensity walking compared with usual care alone. The researcher will provide patients with an intervention booklet which will include: guidance and recommendations to ensure adherence to the intervention; tips and encouragement outlining the benefits of walking; and a diary to keep a log of walking duration and intensity.

In line with recommended guidelines [61], participants will be asked to exercise for 30 minutes five times a week at moderate intensity (defined as walking at a brisk pace). Participants will be encouraged by the researcher to gradually increase walking duration from 10 to 30 minute bouts through the course of the intervention and will be asked to make weekly goals outlining intended exercise intensity, duration and timing (exactly when they intend to exercise). They will be encouraged to reflect upon their achievements or shortfalls from the previous week and to take these into consideration by modifying their goals to ensure they are realistic and achievable. They will also be asked by the researcher to take their chemotherapy schedule into consideration, in order to ensure that they do not over exert themselves or set unrealistic goals during weeks in which they will be receiving treatment. This information will also be presented in the walking booklet. Pedometers will be given to the intervention group at the start of the intervention so that they can be used to measure daily step count and to provide patients with immediate feedback and motivation. Relevant behaviour change taxonomies [62] have been applied to this design in order to allow accurate, reliable replication (Table 1).

